## Abstract

**Background:**

Surgical left atrial appendage (LAA) closure concomitant to open-heart surgery prevents thromboembolism in high-risk patients. Nevertheless, high-level evidence does not exist for LAA closure performed in patients with any CHA_2_DS_2_-VASc score and preoperative atrial fibrillation or flutter (AF) status—the current trial attempts to provide such evidence.

**Methods:**

The study is designed as a randomized, open-label, blinded outcome assessor, multicenter trial of adult patients undergoing first-time elective open-heart surgery. Patients with and without AF and any CHA_2_DS_2_-VASc score will be enrolled. The primary exclusion criteria are planned LAA closure, planned AF ablation, or ongoing endocarditis. Before randomization, a three-step stratification process will sort patients by site, surgery type, and preoperative or expected oral anticoagulation treatment. Patients will undergo balanced randomization (1:1) to LAA closure on top of the planned cardiac surgery or standard care. Block sizes vary from 8 to 16. Neurologists blinded to randomization will adjudicate the primary outcome of stroke, including transient ischemic attack (TIA). The secondary outcomes include a composite outcome of stroke, including TIA, and silent cerebral infarcts, an outcome of ischemic stroke, including TIA, and a composite outcome of stroke and all-cause mortality. LAA closure is expected to provide a 60% relative risk reduction. In total, 1500 patients will be randomized and followed for 2 years.

**Discussion:**

The trial is expected to help form future guidelines within surgical LAA closure. This statistical analysis plan ensures transparency of analyses and limits potential reporting biases.

**Trial registration:**

Clinicaltrials.gov, NCT03724318. Registered 26 October 2018, https://clinicaltrials.gov/study/NCT03724318.

**Protocol version:**

10.1016/j.ahj.2023.06.003.

**Supplementary Information:**

The online version contains supplementary material available at 10.1186/s13063-024-08122-9. The SAP checklist is supplied in the supplementary material.

## Introduction

### Background and rationale

Patients undergoing open-heart surgery generally have many comorbidities and a high prevalence of atrial fibrillation (AF), yielding an elevated risk of stroke compared to the background population [1–5]. The left atrial appendage (LAA) is a highly trabeculated predilection point for thrombus formation, especially during AF, where there is poor atrial contraction and reduced blood flow in the atria [6–8]. The thrombi may dislodge and follow the arterial bloodstream to the brain, causing a stroke [6–8]. In 2018, a randomized clinical trial showed that surgical closure of the LAA resulted in a lower incidence of combined stroke, transient ischemic attack (TIA), and silent cerebral infarction (SCI) compared to leaving the LAA open [9]. Although a trend was noted, the trial was underpowered to answer whether surgical LAA closure protects against stroke and TIA [9]. Other studies suggest that LAA closure performed in addition to open-heart surgery is safe and can reduce the incidence of thromboembolism [10–12]. Accordingly, current guidelines declare that surgical LAA closure may be considered in patients with AF undergoing open-heart surgery (Class IIb) [10–15]. Recently, the largest randomized clinical trial to date reported that surgical LAA closure reduced the risk of systemic thromboembolism and stroke in patients with AF and a high risk of thromboembolism (CHA_2_DS_2_-VASc ≥ 2) [13]. Nevertheless, whether LAA closure is safe and advantageous for patients without AF and a low á priori stroke risk remains unknown [6, 16, 17]. The rationale of the LAACS-2 trial is to provide such evidence. Accordingly, the LAACS-2 trial will evaluate if prophylactic LAA closure as a standard add-on to open-heart surgery is safe and can reduce the risk of stroke and TIA events. The recommended LAA closure is by an epicardial device, with open-heart surgery without LAA closure as the comparator.

### Objectives

#### Primary objective

To test the hypothesis that closure of the LAA concomitantly with elective open-heart surgery can reduce the incidence of stroke compared to leaving the LAA open, regardless of previous AF diagnosis and CHA_2_DS_2_-VASc score.

#### Secondary objectives

To evaluate if the incidence of combined stroke, TIA, and SCI may be reduced by closing the LAA in the same population as above.

To evaluate if the incidence of combined ischemic stroke, TIA, and SCI may be reduced by closing the LAA in the same population as above.

To evaluate if all-cause mortality and stroke incidence can be reduced by closing the LAA in the same population as above.

To evaluate the safety of LAA closure performed concomitantly with elective open-heart surgery in the same population as above.

## Study methods

### Trial design

A randomized, multicenter trial of LAA closure performed during surgery in addition to planned open-heart surgery. The comparator is leaving the LAA open. The preferred method of LAA closure is by an epicardial device (AtriClip®, AtriCure Inc., West Chester, Ohio, USA). Alternatively, a stapler may amputate the LAA at the surgeon’s discretion. After the surgical intervention, there are no limitations in anticoagulant use, heart rate-limiting, or rhythm-controlling treatment, including cardioversion attempts. Adherence to current clinical guidelines is recommended.

### Framework

The hypothesis testing framework is that of a superiority trial. The hypothesis being tested is that LAA closure is superior to leaving the LAA open when concerning the primary outcome. Moreover, that there is no difference between LAA closure and leaving the LAA open when considering safety outcomes. No power calculations have been performed for the safety outcomes.

### Randomization and stratification

Before randomization, a three-step stratification is performed. The first step is “site,” the second is “surgery type,” and the third is “use of oral anticoagulant (OAC)” (see the table below).

### Sample size

Based on previous studies, estimated event rates are 1.2% vs. 3.0% per year for patients with and without LAA closure, respectively [8, 9, 11, 16, 18, 19]. A total of 1302 patients need to be included if they are randomized 1:1, followed for 2 years, and a significance level of 0.05 and 90% power is to be achieved. With these numbers, 16 primary events are expected for patients with LAA closure and 39 for patients with an open LAA. The trial will enroll 1500 patients to account for deviations in treatment allocation and death. Please see the trial protocol for more details [20].

### Statistical interim analyses, safety, and stopping guidance

No interim analyses will be conducted. An analysis and evaluation of adverse events will be performed by the trial Data Safety Monitoring Board annually. The Data Safety Monitoring Board will recommend that the Steering Committee discontinue the trial if there is reasonable concern that LAA closure increases the risk of adverse events.

### Timing of the final analysis

The final analysis is scheduled for when 55 primary events have occurred, which is anticipated once the last patient recruited has undergone 2 years of follow-up (please see section on “sample size”). The Steering Committee will decide whether to shorten follow-up if 55 primary events have occurred before 2 years of follow-up for all patients or before 1500 patients have been enrolled. Contrarily, the Steering Committee may opt to extend follow-up if fewer than 55 events have occurred once the last enrolled patient has 2 years of follow-up.

### Timing of outcome assessments

The primary and secondary outcomes will be assessed at discharge, 3 months after surgery, and then annually until the end of follow-up.

Safety outcomes will be assessed 30 days after index surgery and, subsequently, at the same time intervals as the abovementioned outcomes.

## Statistical principles

### Confidence intervals and *P* values

A significance level of 5% and a confidence interval of 95% will be applied. No multiplicity adjustment is planned; consequently, findings in secondary outcomes are considered exploratory. Only two-sided significance tests will be used.

### Adherence and protocol deviations

Adherence to the treatment assignment denotes whether patients follow the assigned randomization (LAA closure vs. leaving the LAA open). Any patient not following the assigned randomization will be considered a protocol violation. Adherence to the intervention will be presented as a proportion relative to the intended allocation. If LAA closure is performed on a clinical indication during follow-up, the patient’s follow-up will be halted at the moment of closure. Such cases will be reported separately.

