### Analyses of the populations

All outcomes will be analyzed as intention-to-treat (ITT) and per-protocol (PP). In the ITT analyses, the assigned randomization is the basis of the segregation of treatment groups. Only data from patients with LAA status congruent with randomization will be included in the PP analyses.

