### Analysis methods

The respective investigators gather data from each site, and primary and secondary analyses will be performed centrally.

The primary analyses rely on time-to-event (survival) statistics.

The possible events are as follows:I.Primary outcome occurrenceII.DeathIII.Withdrawal of consentIV.Last contact (loss to follow-up)V.Trial end*

*The time frame is at least 2 years from index surgery; thus, follow-up continues for all patients until the last enrolled patient has been followed for 2 years.

The time between randomization and event (I–V) is the exposure time.

The primary analyses will be based on the ITT principle, i.e., it includes all randomized patients with an available baseline assessment independently of the performed surgery.

PP analyses will serve as sensitivity analyses.

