#### Analyses of the primary outcome

Cumulative incidence (Aalen-Johansen) plots will display results of the primary outcome with death as a competing risk. Gray’s test for differences between cumulative incidence rates will be used to assess statistical significance.

As the primary outcome will be examined in a competing risk setting, cause-specific Cox regression is used to quantify the difference in risk between allocation groups. The main covariate is randomization (LAA closure vs. open LAA). The analysis will be adjusted for the stratification factors before randomization, i.e., site, surgery type, and OAC therapy. The results will be presented as hazard ratio (HR) with 95% confidence intervals.

The null hypothesis is that there is no difference between the cumulative incidence rates of the two treatment groups.

The decision rule for the hazard ratio is as follows:

VI.Superiority of LAA closure will be accepted if the estimated HR is < 1 and the 95% confidence interval (CI) does not include 1VII.Superiority of open LAA will be accepted if the estimated HR is > 1 and the 95% CI does not include 1VIII.No superiority will be accepted if the 95% CI contains 1

Proportional hazard assumptions for the Cox regression models will be tested by interaction terms with time on study, weighted Schoenfeld, and cumulative Martingale residuals. If non-proportionality is detected for covariables used for adjustment (site, surgery type, and OAC therapy), these factors will be included as stratification variables. If non-proportionality is detected for the primary exposure (randomization), time-varying hazard ratios with 95% confidence intervals will be used to assess the differential effect of randomization as a function of time-on study.

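### The rule that stops follow-up at a later clinically indicated LAA closure contradicts the ITT primary analysis; the likely numerical effect is small and the repair is cheap

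*SAP article*

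**What the plan says.** Adherence and protocol deviations: when the appendage is closed on a clinical indication during follow-up, "follow-up will be halted at the moment of closure". The next sentence adds "Such cases will be reported separately". The rule stands among the general statistical principles. It names no analysis set, arm, indication or expected number.

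Analyses of the populations: "In the ITT analyses, the assigned randomization is the basis of the segregation of treatment groups".

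Analysis methods: the primary analysis is ITT and "includes all randomized patients with an available baseline assessment independently of the performed surgery". Five events are listed: primary outcome, death, withdrawal of consent, last contact and trial end. Then "The time between randomization and event (I–V) is the exposure time". A footnote says that "follow-up continues for all patients until the last enrolled patient has been followed for 2 years".

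Analyses of the primary outcome: "Cumulative incidence (Aalen-Johansen) plots will display results of the primary outcome with death as a competing risk". No other competing event is named. The planned sensitivity analyses are per-protocol and complete-case.

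**The concern.** A later closure is a change of treatment after randomization. An ITT analysis follows the patient through it and counts what happens in the assigned arm. Stopping at closure answers a different question: the effect while the appendage stays as it was left at surgery, or as if no later closure had occurred. A programmer who reads the list of five events would keep the patient at risk; one who reads the adherence section would censor.

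The rule also stops data collection, so it is more than an analysis convention. These patients have not withdrawn consent, yet their later strokes and deaths would not be gathered.

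Two further points are plausible, but they are inference. A patient whose appendage is already closed has little scope for another closure, apart from non-adherence or failed closure, so the censoring would probably fall mostly on the open-LAA arm. The SAP's rationale for closure is stroke prevention, so a clinical indication probably tracks stroke risk. If both hold, the censoring is one-sided and not independent of the outcome.

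**Working it through.** **1. The texts side by side**

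| Question | Adherence and protocol deviations | Analysis methods |
|---|---|---|
| What ends a patient's time at risk? | Later clinically indicated closure | One of five events; later closure is not among them |
| How long are patients followed? | Until that closure | All patients, until the last enrolled has two years |
| Which analysis? | Not limited to any | ITT, as the primary analysis |

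The direct conflict is with the list of five events and the rule on length of follow-up.

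**2. The plan's own figures (Sample size)**

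Inputs are 1.2% and 3.0% per year, two years, 1:1 allocation, two-sided 5% and 90% power. The pooled two-proportion formula with risks 0.024 and 0.060 gives 651 per arm, or 1302 in total, which matches the plan. Events are 651 × 0.060 = 39.1 and 651 × 0.024 = 15.6, that is 39 + 16 = 55. The concern changes none of these.

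**3. Size of the effect, under assumptions**

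The SAP gives no later-closure rate. Assume:
- a fraction f of 651 open-arm patients is closed at a time uniform over two years;
- their stroke hazard is r times that of other open-arm patients, with the arm's average baseline hazard held at 3% per year;
- the hazard is multiplied by 0.4 after closure (the plan's 60% reduction);
- the closure arm has 1.2% per year, and deaths are ignored.

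With constant hazards and no closures, the open arm expects 651 × (1 − e^−0.06) = 37.9 events. HR is the ratio of event rates. Simulated results:

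| f | r | Events, followed on | Events, censored | HR, followed on | HR, censored |
|---|---|---|---|---|---|
| 1% | 1 | 37.9 | 37.8 | 0.400 | 0.399 |
| 1% | 5 | 37.4 | 37.0 | 0.406 | 0.408 |
| 2% | 1 | 37.7 | 37.6 | 0.402 | 0.400 |
| 2% | 5 | 36.7 | 36.1 | 0.413 | 0.417 |
| 5% | 1 | 37.5 | 37.1 | 0.405 | 0.399 |
| 5% | 3 | 36.4 | 35.4 | 0.417 | 0.418 |
| 5% | 5 | 35.4 | 33.9 | 0.429 | 0.437 |

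Exact check of the last row:
- Baseline hazards are 0.03 / (0.95 + 0.05 × 5) = 0.025 for the others and 0.125 for the closed group.
- Others: 618.45 × (1 − e^−0.05) = 30.16 events.
- Closed group (32.55 patients), censored: 32.55 × [1 − (1 − e^−0.25)/0.25] = 3.75 events.
- Closed group, followed on: 32.55 × [1 − e^−0.1 × (1 − e^−0.15)/0.15] = 5.20 events.
- Totals are 33.9 and 35.4, so 1.45 events are lost.

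The direction depends on r. At r = 1, censoring removes the dilution from crossover and the HR moves away from 1. At r = 5, it removes high-risk patients and the HR moves towards 1.

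**4. Could the conclusion change?**

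Use the approximate 95% limit, ratio × exp(1.96 × √(1/a + 1/b)), with equal person-time unless stated.
- 16 vs 39 events: ratio 0.41, upper limit 0.73.
- 16 vs 37: ratio 0.43, upper limit 0.78.
- 23 vs 39 (a borderline result): ratio 0.59, upper limit 0.99.
- 23 vs 37: upper limit 1.05. If 3% of open-arm person-time is removed as well, 0.622 × 0.97 = 0.603 and the limit is about 1.01.

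At the planned effect the conclusion stands. A result already close to the boundary could cross it.

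**5. Which outcomes are touched**

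Only the first adjudicated primary event counts, so closure after a first stroke or TIA leaves the primary outcome unchanged. The composite of death and stroke excludes TIA, so closure after a TIA would censor it. Closure after either event would censor all-cause mortality.

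**The case against.** The strongest reply is that late closures are probably rare, the article promises to report them separately, and the modelled shift in HR is about 0.01. If closure is unrelated to risk, censoring adds essentially no bias to the cause-specific hazard. Closures prompted by a first stroke or TIA do not reach the primary outcome. The sentences on grouping by assignment and on including all randomized patients are not strictly breached either, because halting follow-up neither moves nor excludes anyone. All of this stands, and it limits the size of the point. It does not remove the conflict with the five listed events and the follow-up rule. Separate reporting discloses the cases without restoring ITT, and neither planned sensitivity analysis tests the effect of censoring at closure.

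A reader might infer more than the documents support:
- **That up to 10 events are lost.** 750 × 0.05 × 0.09 × 3 = 10.1 needs 5% closed, three times the open-arm rate continuing after closure with no benefit, and three years remaining. With the plan's 60% reduction the rate is 0.036 per year, giving 750 × 0.05 × 0.036 × 3 = 4.1. With one year remaining on average, as in a two-year window, it is 1.4. Person-time is lost too, so a count of events overstates the bias.
- **That a few lost events would overturn the planned result.** Step 4 of the working shows otherwise.
- **That ITT is beyond recovery.** Chart review could recover the events. Record review at 5 and 10 years is already intended, although the article does not say whether halted patients are included.
- **That the censoring is known to be informative and confined to the open arm.** The SAP states no arm, indication or rate.

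**Conclusion.** The point holds as a contradiction in the primary analysis. The adherence section stops follow-up at later closure, while the analysis section requires ITT follow-up of all patients and does not list closure as an end of exposure. If the halting rule is followed, the result reported as ITT is a censored-at-crossover result.

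The expected size is small: about 0.1–1.5 of roughly 38 open-arm events and at most about 0.01 on the HR, with no predictable direction. That rests on 1–5% of the open arm being closed later, one to five times the stroke hazard in those patients, a 60% reduction after closure, and a two-year horizon. More closures or longer remaining follow-up would enlarge it. It matters because the decision rule turns on whether the confidence interval contains 1, and because data not collected must be retrieved later.

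**What to change.** Reconcile Adherence and protocol deviations with Analysis methods before the final analysis:
- For ITT, continue chart follow-up after any later closure and count events in the assigned arm, for the primary, secondary and mortality outcomes.
- Censor at later closure only in the per-protocol analysis or a named sensitivity analysis.
- Report the number and dates of later closures by arm.
- For patients whose follow-up has already been halted, recover events by chart review where consent allows.

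The cost is a change of SAP wording and continued chart follow-up for what is probably a small number of patients. The 1302 patients and 55 events stay as they are, and nothing in clinical care changes.

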### Analyses of the populations

All outcomes will be analyzed as intention-to-treat (ITT) and per-protocol (PP). In the ITT analyses, the assigned randomization is the basis of the segregation of treatment groups. Only data from patients with LAA status congruent with randomization will be included in the PP analyses.

## Trial population

### Screening data

Patients referred for elective open-heart surgery at each site will be screened for eligibility. Sites register the total number of screened patients, whether in- and exclusion criteria have been met, and whether exclusion is due to patient dissent to study participation or planned LAA closure. Summed screening data will be presented in the main publication.

### Eligibility

#### Inclusion criteria

Patients ≥ 18 yearsElective open-heart surgery (CABG, valve, or combined)Signed informed consent

#### Exclusion criteria

Prior open-heart surgeryCurrent endocarditisPlanned closure of the LAAPlanned ablation for AFFollow-up impossible

### Recruitment

Recruitment data will be presented in a Consolidated Standards of Reporting Trials (CONSORT) flow diagram. The diagram will include data on the estimated number of patients assessed for eligibility per site and the number of patients excluded, including reasons. Furthermore, the number of patients randomized and the two allocation groups (including data on whether patients received the allocated intervention as intended) will be shown. Subsequently, any loss to follow-up and patients excluded for other reasons will be displayed, leaving the final dataset available for analysis.

### Withdrawal/follow-up

Patients may retract their consent at any time point during follow-up. The intervention cannot be undone; therefore, retraction of consent after surgery entails that follow-up data will no longer be gathered. If consent is retracted, the date will be registered, and data will be included in the analysis until this date if accepted by the patient. Alternatively, all data will be deleted if requested by the patient. In this case, data will not be included in the analysis. The number of patients retracting consent and their reasons will be presented in the CONSORT flow diagram.

### Baseline patient characteristics

The following baseline patient characteristics will be presented:

I.Demographics: age and sexII.Measurements:◦ Optional: height, weight, blood pressure, left ventricular ejection fraction, and estimated glomerular filtration rateIII.Comorbidities: prior stroke, TIA, AF, or atrial flutter◦ Optional: ischemic heart disease, peripheral artery disease, cardiac valve disease, congestive heart failure, pacemaker or implantable cardioverter defibrillator implantation, hypertension, chronic obstructive/restrictive pulmonary disease, diabetes mellitus, chronic kidney disease, autoimmune disease, active cancerIV.Medications: any heart rhythm or frequency modulators, anticoagulation, or antiplatelet therapyV.Prior brain scans: any brain scan performed before study enrolment, including findings

Continuous variables will be summarized as mean (standard deviation) or median (interquartile range), while categorical variables are summarized as frequencies (percentages).

